###### Sleep Variability

The Actigraph device is a small, noninvasive device worn on the nondominant wrist that records limb movements using electrical impulses, and it has been validated for use in people with insomnia [110]. Sleep parameters including SE, SL, TST, and WASO will be measured. In addition to the Actigraph, we will also use a sleep diary to allow for better estimation of the time in and out of bed as well as for removing invalid sleep periods that are measured by the Actigraph [111]. The sleep diary will also measure total time spent in bed, total time spent out of bed, number of awakenings, number of bathroom visits, and glucose level before and after sleep time. All sleep parameters will be presented in averages of 7 nights and the coefficient of variance (CV) will be calculated using the following equation (CV=standard deviation/mean×100) for each objective and subjective sleep parameters—SE, SL, TST, and WASO—to analyze objectively within-subject variability of nighttime sleep of 7 nights. This calculation will provide a percentage value with a higher number suggesting higher variability [112].

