##### Statistical Methods

A chi-square test will be used to compare between-group differences in categorical variables. Independent 2-sample *t* tests will be used to compare differences in continuous between-group demographic characteristics and clinical variables.

For the main analysis**,** the effect of the CBT-I intervention will be investigated by calculating change scores for the insomnia severity; DSCB; A_1c_; fatigue; sleep quality; daytime sleepiness; and symptoms of depression, anxiety, and pain. In addition, for variability of each sleep outcomes (SE, SL, TST, and WASO), CV of 7 nights before the pre- and postintervention assessments will be calculated, and change scores will be calculated. Then, independent sample *t* tests will be utilized to investigate the between-group difference in the change score means of all outcomes. A completer vs noncompleter analysis will be performed. For all analyses, alpha level will be set at .05.

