Owing to the complex relationship between insomnia and T2D, some factors are needed to be controlled to fully investigate the relationship. Owing to the small sample size and possible covariates that might not be included in the power calculation, these complex relationships will be investigated using exploratory analyses. Post hoc analysis using the type and number of medications will used to address the potential confounding effects on the outcomes. Univariate linear regression will be used to control for demographic and clinical variables (covariates). The decision to perform these analyses with demographic and clinical variables will be made if there are significant between-group differences at baseline in depression symptoms, anxiety symptoms, pain symptoms, gender, diabetes duration, or body mass index. Mixed models will be used to account for the correlation between times in pre- and posttest (7 nights as random factor) sleep variability (as dependent variable) and facilitate adjustment for covariates to compare the difference in sleep variability between the CBT-I and HE groups (groups as fixed factor). Covariates will be determined if there is a difference in the baseline assessment for demographic and clinical outcomes. Those participants who are treated with CPAP will be asked to report their compliance using CPAP during baseline and postintervention assessments. Subjects who are using VPAP will be given a modified sleep diary to check off nights of CPAP compliance during the assessment sessions. An exploratory subanalysis will be utilized to investigate the difference in insomnia severity between compliance and noncompliance with CPAP. Noncompliance is defined as (1) missing more than 2 nights during the 7 nights period that the participant is wearing the Actigraph or (2) using the CPAP for <4 hours per night during this study.

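### The exploratory mixed model for sleep variability names nights as its random factor, but the outcome has only one value per seven-night period

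*Protocol article*

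**What the plan says.** The Sleep Variability section of the Protocol article defines the outcome: "All sleep parameters will be presented in averages of 7 nights and the coefficient of variance (CV) will be calculated using the following equation", namely standard deviation over mean times 100. This is done for each objective and subjective parameter (sleep efficiency, sleep latency, total sleep time and wake after sleep onset). The aim is to describe "within-subject variability of nighttime sleep of 7 nights".

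The Statistical Methods section then gives two analyses of this outcome.

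- **Main analysis.** "CV of 7 nights before the pre- and postintervention assessments will be calculated, and change scores will be calculated", after which "independent sample *t* tests will be utilized to investigate the between-group difference in the change score means of all outcomes".
- **Mixed model.** The next paragraph, which says of the covariate questions that "these complex relationships will be investigated using exploratory analyses", adds mixed models to "account for the correlation between times in pre- and posttest (7 nights as random factor) sleep variability (as dependent variable"). They are also meant to allow covariate adjustment and to "compare the difference in sleep variability between the CBT-I and HE groups (groups as fixed factor").

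The description names no participant effect, no time term, no group-by-time term and no baseline CV as covariate.

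**The concern.** The random factor and the dependent variable belong to different levels of the data. A night factor needs one row per night. The CV is a summary that has already used up the seven nights, so it has one row per participant and period. The two stated elements cannot both hold in an ordinary mixed model.

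The sentence also misses its own aim. Correlation between a person's pre and post values needs a participant random effect, or an equivalent within-participant covariance. Nights do not supply it.

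Finally, if both periods are outcomes and the groups are compared through a group main effect, that effect mixes a period before treatment with a period after it. At stake is whether an analyst working from this text could fit a model whose named term is the treatment effect on sleep variability.

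**Working it through.** The article gives no figure for this model, so there is none to reproduce.

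**Inputs from the article.** CV = SD/mean × 100 over 7 nights (Sleep Variability); one CV before and one after the intervention (Statistical Methods); 14 participants per arm (Allocation Sequence Generation); alpha .05 (Statistical Methods). All effect sizes, SDs and correlations below are assumptions, because the article gives none for sleep variability.

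**1. Count the rows.** Seven pre nights give 1 CV and seven post nights give 1 CV, so there are 2 rows per participant for each parameter. None is indexed by night.

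**2. Try nightly values instead.** With 7 + 7 = 14 nightly rows per participant a night factor has rows, but the outcome becomes the level of sleep, not its variability. To illustrate, nightly total sleep time was simulated for 200 participants per arm (mean 380 min, between-person SD 40, night-to-night SD 60), with treatment halving the night-to-night SD and leaving the mean unchanged. The group-by-time term on nightly values was 3.9 (SE 2.9), compatible with its true value of 0. Over the same data the mean CV in the treated arm fell from 14.7 to 7.7, against 15.1 to 14.9 in the control arm. The nightly mean model does not see a large change in variability.

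**3. What the group coefficient estimates.** Let δ be the treatment effect on post CV. Randomization makes the expected pre difference 0. With complete pairs and group as the only fixed factor, the group coefficient is the between-group difference in person means (pre + post)/2:

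- group only: (0 + δ)/2 = δ/2
- change score: δ − 0 = δ

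The halving depends on no assumed SD.

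**4. Numerical check.** Assume δ = −10 CV points, between-person SD 8, within-person SD 6 and 14 per arm. The total variance is 64 + 36 = 100, so δ is 1 SD and the pre-post correlation is 64/100 = 0.64.

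- Change score: SD = √(2 × 36) = 8.49; SE = 8.49 × √(2/14) = 3.21; ratio 10/3.21 = 3.12.
- Group only: SD of the person mean = √(64 + 36/2) = 9.06; SE = 9.06 × √(2/14) = 3.42; ratio 5/3.42 = 1.46.

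Over 5,000 simulated trials, with critical value 2.056, the change-score difference averaged −9.98 with power 0.85. The group-only coefficient averaged −4.98 with power 0.28. In one large data set (200 per arm), a fitted mixed model with a participant intercept gave −5.00 for group alone and −9.41 for group-by-time.

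**5. Range over the pre-post correlation r** (14 per arm, assumed 1-SD effect, 5,000 replicates), power:

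| r | group only | group-by-time | ANCOVA on baseline CV |
|---|---|---|---|
| 0.3 | 0.36 | 0.58 | 0.75 |
| 0.5 | 0.31 | 0.72 | 0.82 |
| 0.7 | 0.29 | 0.91 | 0.93 |

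With complete pairs and no covariates, group-by-time with a participant intercept matches the t test on change scores, so the middle column also describes the test already planned as the main analysis. The last column differs from it, so ANCOVA is not the same analysis.

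**The case against.** Three points can be made in the plan's defence.

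**The model is exploratory and the main test is sound.** This stands in full. The t test on change in CV is well defined and targets δ. A reader might infer that the sleep-variability conclusion is at risk, or that the trial gives up the power gap in the table. The article supports neither: the group-by-time power belongs to a test that is already the main analysis.

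**A journal article need not list every model term.** This stands in part. Calling group a fixed factor labels its role and need not be an exhaustive model statement. The mention of correlation between pre and post suggests that a repeated-measures structure is intended. Missing time, interaction and participant terms would be a weak point on their own, and the halving applies only if the description is taken literally. The night factor is different: it is stated, and a fuller plan could not reconcile it with a once-per-period CV in an ordinary mixed model without changing what is written.

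**The model would run once the night factor is dropped.** True. It would then run with a group term that targets half the effect, unless the other terms are added.

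A reader might also infer inflated false positives from analysing 14 nightly rows per person without a participant effect. That would concern nightly sleep levels under an assumed intraclass correlation that the article does not give. It is not an error rate for the CV outcome and forms no part of this point.

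**Conclusion.** The point holds in a limited form. The stated random factor does not fit the stated dependent variable, and the participant, whose repeated measurement creates the pre-post correlation, is not named in its place. This follows from the article's own definitions and needs no assumption.

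The consequence for the group coefficient is conditional. If both periods are outcomes and group is the only fixed factor besides covariates, it estimates half the post-treatment difference. The factor of one half is algebra and assumes only randomization and complete pairs. The power figures also rest on normally distributed CVs, a 1-SD effect and the assumed correlations.

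The defect is confined to an exploratory model. It does not touch the change-score t test on CV or the primary analysis of insomnia severity. It is worth correcting because, as written, the model cannot be fitted to the outcome it names.

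**What to change.** Replace the night factor with a participant random intercept. State that the dependent variable is the CV per participant and period, with fixed effects for group, time and group-by-time plus any chosen covariates, and that group-by-time is the treatment effect. With complete pairs, a covariate that is constant over both periods alters that term only if its product with time is also entered, so the text should say how covariates enter.

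Alternatively, specify ANCOVA of post CV on baseline CV, with group and covariates. It has one row per participant, adjusts for covariates directly and is generally more powerful. It should be presented as a different analysis from the change-score comparison, not as its equivalent.

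If nightly data are wanted, a location-scale mixed model with group-by-time in the residual variance would address variability. This is optional, and demanding for 28 participants.

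The cost is analysis wording and code only. No new data are needed.

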##### Monitoring and Ethics

###### Data Monitoring

The primary investigator will review the dataset at least semiannually. The primary investigator’s evaluation will be focused on the quality of data collection and data management. In addition, the investigators will review data in an ongoing manner for accuracy, both at a time when these data are entered into the database and during analysis.

###### Harms

During the pre and postassessment sessions, testing will be stopped if the subjects show signs of low blood sugar (<70 mg/dL) or if signs of dizziness or headache are noted by the assessor or reported by the participant. During assessment sessions, participants also will be instructed to stop the test at any time for a rest break, as often as needed.

There is a risk of skin redness may be associated with wearing the Actigraph for 1 week. The risks of wearing the Actigraph are nearly the same as wearing a wrist watch. If skin redness or inflammation happened, subjects may remove the Actigraph and immediately report the symptoms to research personnel. In addition, there is a risk of minor electrical shock if the Actigraph is damaged. If damage to the Actigraph occurs, subject will be asked to return it to our lab, and they will be given a replacement.

Initially, participating in a CBT-I intervention may have an increase in sleepiness, which may impact participants’ fatigue, thinking ability, or functional abilities. It is anticipated that this increase in sleepiness will be temporary and should help participants sleep better in the long term.

During the in-person screening session, if suicidal intent is identified through either the BDI (question number 9, with a *2* or a *3*) or verbal statement from the participant, a suicidality protocol will be followed. The suicidality protocol is designed to provide the researcher with contact information for appropriate psychology and psychiatric professionals at KUMC.

####### Research Ethics Approval

The study will be performed in accordance with KUMC’s Institutional Review Board and Human Subjects Committee. No individuals will be excluded based on sex, race, or ethnicity. Interested participants will be administered a structured screening interview to determine their eligibility for the study. During the consent session, all interested participant will be informed about the study’s objective, risks, procedure, and potential benefits (or lack thereof).

######## Consent or Assent

Consent will be obtained in Georgia Holland Health Exercise and Aging Lab on the main campus of KUMC. Participants will be encouraged to ask any questions about the study as much as they need, and members of research study will answer their questions. In addition, participants will be informed if there is any change in the protocol to sign a new consent form.

######## Confidentiality

All data will be deidentified and stored on the KUMC research private drive, which will be secured and backed up every night. The working dataset will be stored on a password-protected computer in the primary investigator’s laboratory, with access restricted to study researchers who are actively working with these data. All subject files and documents will be stored in a locked cabinet.

## Results

A total of 28 participants with T2D and insomnia symptoms recruited from February 2019. This study currently completed the recruitment stage. The completion date for the study was September 2019. Our results will describe the changes in insomnia severity; sleep variability; fatigue; A_1c_; DSCB; and severity of depression, anxiety, and pain. We will report our results in tables and figures using SPSS and GraphPad, respectively.

## Discussion

### Overview

Our study will be the first in conducting an RCT using CBT-I for people with T2D. If this study indicates that 6 sessions of CBT-I are effective in improving sleep and diabetes outcomes in people with T2D and insomnia symptoms when compared with HE, CBT-I could be implemented as an effective and safe treatment for this population, although more research will be needed to verify the findings of this pilot RCT.

Pharmacological interventions for sleep difficulties have shown harmful effects on people with T2D. There is a need to better understand safe intervention benefits in people with T2D. This study will contribute to the management of T2D using behavioral sleep intervention as an effective and safe treatment for people with insomnia symptoms. The results will contribute to the literature by examining the effect of CBT-I on both sleep and diabetes outcomes. This will help in understanding the effectiveness of short duration intervention designed for people with insomnia symptoms.

### Strengths

The study strengths include utilizing important methods for people with T2D, such as objective measures, design, and safe intervention. Determining sleep variability using objective and subjective measures will accurately detect sleep improvement after an intervention. Using comparative groups to understand the effect of CBT-I on insomnia symptoms, sleep variability, fatigue, and diabetes-related health outcomes will add new information to the literature and improve the understanding of clinical conditions. Previous studies recommend optimizing the sleep quality and quantity for people with comorbidities. Understanding the effect of CBT-I in people with T2D will expand the generalizability of using this type of interventions.

### Limitations

Some limitations in this protocol might be important to consider in future studies. First, we will not confirm the diagnosis of T2D using the current American Diabetes Association guidelines. However, a study showed that the specificity of prevalent self-reported diabetes and incident self-reported diabetes were 84% and 97% and sensitivity of 55% and 80%, respectively, compared with fasting glucose, A_1c_, and/or medication use [100]. In addition, a study suggests that self-report of diabetes is sufficiently accurate [101]. To overcome this limitation, we will review the medication list to confirm T2D diagnosis during the in-person screening visit. Second, we might not able to distinguish the improvement in insomnia severity between controlled vs uncontrolled diabetes, which might be examined under future sleep behavioral therapy studies. Third, our study will be powered based on the ISI, and we recommend future studies to choose a diabetes outcome for conducting the power calculation. Fourth, the participants will not be blinded in the study, which may result in the control group participants looking for CBT-I providers outside of the study. We will monitor any change in pharmacological or nonpharmacological treatments during the postintervention session to help explain unexpected results. It is possible, however, that some participant may not reveal this information, which might influence the outcomes. Finally, we will not be able to monitor CPAP compliance during the intervention, but we will follow up with people in the CBT-I group to ensure no issue wearing a CPAP machine every session.

## Abbreviations

A_1c_: glycemic control
BDI: Beck Depression Inventory
BPI: Brief Pain Inventory
CBT-I: cognitive behavioral therapy for insomnia
HE: Health Education
CV: coefficient of variance
DCP: diabetic care profile
DSCB: diabetes self-care behavior
ESS: Epworth Sleepiness Scale
FSS: Fatigue Severity Scale
GAD-7: Generalized Anxiety Disorder–7
HPA: hypothalamic-pituitary-adrenal
ISI: Insomnia Severity Index
KUMC: University of Kansas Medical Center
CPAP: continuous passive airway pressure
PSQI: Pittsburgh Sleep Quality Index
RCT: randomized controlled trial
RLS: restless leg syndrome
SE: sleep efficiency
SL: sleep latency
STOP-Bang: snoring, tiredness, observed apnea, blood pressure, body mass index, age, neck circumference, and gender
T2D: type 2 diabetes
TNF: tumor necrosis factor
TST: total sleep time
WASO: waking after sleep onset
